### Outcomes

#### Primary Study End Points: Feasibility and Acceptability

To assess feasibility and acceptability, we will use a realist evaluation approach [38]. Realist evaluation emphasizes the interplay of contexts through social interactions that engage with the intervention. In alignment with this method, this study aims to assess the effects and influences of the digitally provided OT program on the health status of the study participants and the feasibility and acceptance of both digital approaches from the user’s perspective. Therefore, we will collect quantitative data regarding participant rates in the follow-up examinations, participant surveys, and qualitative in-depth interviews about the participants’ participation experiences.

All participants in both intervention groups (n=80) will be asked via email to complete an online questionnaire with four closed (Likert-scaled) questions and two open questions on handling the digital intervention after each of the six intervention modules. This approach will enable the individual evaluation of different program parts. Questions include: “Were you able to apply the content of the last module in your everyday life?” “What was particularly beneficial for you in the last module?” and “How satisfied were you with the last module?”.

Moreover, all participants will be asked to complete an online questionnaire including 35 Likert-scaled items developed within discursive circles by research team members based on the theoretical framework of acceptability (TFA) [39,40]. The TFA proposes a theoretical framework for assessing the acceptability of health interventions and consists of seven component constructs: affective attitude, burden, ethicality, intervention coherence, opportunity costs, perceived effectiveness, and self-efficacy [40].

To enrich quantitative data with the first-hand experiences of the study participants, a subsample of at least 12 study participants of intervention groups 1 and 2 will be invited to share their personal experiences regarding the acceptability and feasibility of the program at week 6 and week 12. These semistructured interviews will last approximately 45 to 60 minutes.

To capture the occupational therapists’ experiences with OT teletherapy, an online focus group interview will be conducted with all occupational therapists working in the study (N=8). A moderation guide will be developed to help facilitate the engagement of participants in a discussion on the feasibility of the treatment concept, acceptance, and recommendations for further intervention development. All conducted interviews, as well as the audio-recorded focus group meeting, will be transcribed according to the simplified rules of Dresing and Pehl [41] and will be analyzed using thematic content analysis [42] by a team of three researchers.

#### Secondary End Points

Secondary outcomes will involve the analysis of possible efficacy outcomes such as cognitive performance, health-related QoL, social participation, occupational performance and satisfaction in daily life, and memory and concentration abilities. All measurements used for data collection and the time points at which they will be collected are depicted in Table 1.

### Analytical Approach

#### Power and Sample Size

The main focus of this study is to assess the feasibility and acceptability of the intervention. Therefore, efficacy analyses with regard to secondary outcomes will only be exploratory. The pilot study is not sufficiently powered to evaluate the effectiveness of the intervention. However, exploratory analyses will address potential differences in outcomes of cognitive function, QoL, occupational performance, and social participation between the intervention and control groups. No previous reports on OT concepts in PCS or online OT in general were available that could have been used to estimate sample sizes. As current practice standards suggest that formal sample size calculations are unsuitable for feasibility trials, the convenience sample of 120-150 participants was selected pragmatically [43].

#### Statistical Analysis Plan

All quantitative data will be prepared using Microsoft Excel or SPSS software and analyzed with R statistical packages. Data visualizations will be created using GraphPad Prism and R software tools. Analysis of the following items is planned from the time points 0 weeks (T0), 12 weeks (T1), and 24 weeks (T2): impairments in daily life activities, family and social life, stress, and sexual activity, and deficits in concentration, attention, and mental speed, particularly focusing on visual attention, physical, mental, and social symptoms of PCS, including concentration, attention, mental speed, mobility, self-care, usual activities, pain, disabilities, anxiety, and depression. An intention-to-treat approach will be used. Estimates and 95% CIs will be computed for the mean, median, and selected lower quantiles. To compare time points, *t*, Wilcoxon-Mann-Whitney, and Kolmogorov-Smirnov tests will be applied, including corrections for multiple testing. Scores derived from questionnaires will be analyzed concerning change over time using *t* and Wilcoxon-Mann-Whitney tests, including corrections for multiple testing. Effect sizes will also be computed. Furthermore, at T0, T1, and T2, we will assess whether certain factors such as age or education influence the feasibility of therapy experiences using *t*, Wilcoxon-Mann-Whitney, and Fisher exact tests as appropriate.

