### Study Design

This pilot study is a 12-week unblinded randomized controlled trial with two intervention groups (group 1: teletherapy/live online; group 2: video on demand) in comparison to a control group (group 3: watch and wait). The study is designed to evaluate feasibility and acceptability, as well as to obtain preliminary evidence on efficacy. The observational period comprises 24 weeks: a baseline assessment (T0) and a 12-week intervention phase with subsequent online questionnaire and testing (T1). At week 24 (T2), study participants will be asked to fill out questionnaires and participate in interviews, and a second round of online testing will be conducted. Given the digital nature of ErgoLoCo, the entire study process, including enrollment, treatment, interviews, and testing, will be performed through online visits.

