**Neurocognitive and occupational impairments (secondary outcomes)**			
	Self-perception of occupational performance in everyday life	Canadian Occupational Performance Measure [27]	Enrollment and week 12
	Memory and cognitive impairment	Wilde-Intelligence test-2, modules MF^a^ and ER^b^ [28]	Enrollment, week 12, and week 24
	Impairment in daily life activities, family and social life, stress, and sexual activity	Index for the Assessment of Health Impairments [29]	Enrollment, week 12, and week 24
	Physical, mental, and social effects of neurological conditions	Quality of Life in Neurological Disorders [30]	Enrollment, week 12, and week 24
	Deficits in concentration, attention [31], and mental speed	D2 test of attention-revised [31]	Enrollment, week 12, and week 24
	Mobility, self-care, usual activities, pain, disabilities, anxiety, and depression	EQ-5D-5L [32]	Enrollment, week 12, and week 24

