### Intervention Delivery

After randomization, each participant is interviewed by an occupational therapist to assess occupational performance challenges in their everyday occupations, using the German version of the Canadian Occupational Performance Measure (COPM) [27]. The COPM has been validated in various OT intervention studies, which provides metrics on changes in occupational performance, satisfaction and importance, and enhancing transparency in OT outcomes [26,34-37].

The teletherapy/live online group (group 1; n=40) will undergo online OT by a professional occupational therapist via teletherapy twice week using the medical communication and conference software medflex, which ensures data security compliant with the German General Data Protection Guidelines, Datenschutz-Grundverordnung. Video group participants (group 2; n=40) will receive digital OT through prerecorded videos twice weekly. Group 2 participants will receive emails every 2 weeks with links to four online videos illustrating the next intervention module. The participants in this group are asked to watch two videos per week. Intervention groups 1 and 2 will receive both a printed and digital version of a workbook that visualizes and supports all tasks performed throughout the program. The control group (group 3; n=80) is a watch-and-wait group, and these participants will receive the video-on-demand- materials after study completion.

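### Two independent-sample tests (Wilcoxon-Mann-Whitney, Kolmogorov-Smirnov) are assigned to comparing time points in the same participants; the error is conservative and confined to exploratory outcomes

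*Protocol article*

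**What the plan says.** The Statistical Analysis Plan section of the protocol article gives two instructions that bear on repeated measurements.

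- The first opens "To compare time points", lists the t test, and continues "Wilcoxon-Mann-Whitney, and Kolmogorov-Smirnov tests will be applied, including corrections for multiple testing".
- The second reads "Scores derived from questionnaires will be analyzed concerning change over time using" t and Wilcoxon-Mann-Whitney tests, again with multiplicity correction.

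The section names no signed-rank test and no mixed or other repeated-measures model. It does not say whether the t test is paired.

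The design is longitudinal within person. Table 1 schedules every secondary instrument except the Canadian Occupational Performance Measure at "Enrollment, week 12, and week 24"; that measure is taken at enrollment and week 12. Study Design confirms that the same people return: "At week 24 (T2), study participants will be asked to fill out questionnaires and participate in interviews, and a second round of online testing" is planned for the cohort already tested at T0 and T1.

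Power and Sample Size describes the efficacy analyses as exploratory and states that the pilot is not powered for effectiveness. Feasibility is the primary objective.

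**The concern.** The Wilcoxon-Mann-Whitney test and the two-sample Kolmogorov-Smirnov test take their null distributions from two independent samples. Scores from one person at T0 and T1 are not independent: someone who scores low at enrollment will usually score low again at week 12. A test that treats the two time points as separate groups leaves all the between-person variation in its error term, whereas a paired test removes it.

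Two things follow when the correlation is positive. The stated significance level is not the true one, and a real change is harder to detect. This pilot is meant to give preliminary evidence on efficacy, and the protocol says that no earlier reports were available to guide sample size. An unnecessary finding of no change could therefore mislead the planning of a later trial. The planned multiplicity correction does not help: it adjusts for the number of tests, not for ignored pairing.

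**Working it through.** **No stated figure to reproduce.** The protocol gives no power, effect size, within-person correlation or alpha for these tests.

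**Inputs from the protocol**
- Group sizes from Intervention Delivery: 40 in each intervention group, and "The control group (group 3; n=80) is a watch-and-wait group". These sum to 160, while Participants and Power and Sample Size give 120 to 150. The calculation uses 40 and 80 with no dropout.
- The comparison is between time points in the same participants.

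**Assumptions**
- Two-sided alpha 0.05.
- Within-person correlation ρ of 0.3 to 0.8, with ρ=0 as a check.
- Change d of 0.3 or 0.5 SD.
- Normally distributed scores with equal SD at both time points.

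**Step 1: why the size is wrong.** With SD 1, the mean within-person difference has variance 2(1−ρ)/n. An unpaired test takes it to be 2/n, so its standard error is too large by a factor 1/√(1−ρ). For a test on means:
- True size = 2 × [1 − Φ(1.96/√(1−ρ))]. At ρ=0.5: 2 × [1 − Φ(1.96/0.707)] = 2 × [1 − Φ(2.772)] = 0.0056.
- Unpaired power = Φ((d/√(2/n) − 1.96)/√(1−ρ)). At n=40, d=0.3, ρ=0.5: d/√(2/n) = 0.3/0.2236 = 1.342, so Φ((1.342 − 1.96)/0.707) = Φ(−0.874) = 0.191.
- Paired power = Φ(d/√(2(1−ρ)/n) − 1.96) = Φ(1.342/0.707 − 1.96) = Φ(−0.063) = 0.475.

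**Step 2: simulation of the named tests** (4,000 replicates per setting). True size at nominal 0.05, n=40:

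| ρ | Wilcoxon-Mann-Whitney | Kolmogorov-Smirnov | Signed-rank |
|---|---|---|---|
| 0 | 0.047 | 0.055 | 0.047 |
| 0.3 | 0.018 | 0.025 | 0.047 |
| 0.5 | 0.008 | 0.016 | 0.054 |
| 0.7 | 0.001 | 0.005 | 0.044 |
| 0.8 | 0.000 | 0.000 | 0.044 |

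The tests are correct at ρ=0 and become more conservative as ρ rises. At n=80 the pattern is the same (Wilcoxon-Mann-Whitney 0.0225, 0.0045 and 0.0005 at ρ = 0.3, 0.5 and 0.7).

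**Step 3: power, Wilcoxon-Mann-Whitney against signed-rank.** Relative loss = 1 − ratio of the two powers.

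| n | d | ρ=0.3 | ρ=0.5 | ρ=0.7 | ρ=0.8 |
|---|---|---|---|---|---|
| 40 | 0.3 | 0.22 v 0.34 (36%) | 0.18 v 0.45 (60%) | 0.14 v 0.66 (79%) | 0.10 v 0.82 (88%) |
| 40 | 0.5 | 0.58 v 0.71 (18%) | 0.60 v 0.85 (30%) | 0.64 v 0.97 (34%) | 0.65 v 1.00 (34%) |
| 80 | 0.3 | 0.44 v 0.60 (26%) | 0.44 v 0.74 (41%) | 0.40 v 0.91 (56%) | 0.41 v 0.98 (58%) |
| 80 | 0.5 | 0.90 v 0.95 (5%) | 0.94 v 0.99 (5%) | 0.98 v 1.00 (2%) | 0.99 v 1.00 (1%) |

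At n=40, d=0.3, ρ=0.5 the simulated 0.18 and 0.45 sit close to the 0.191 and 0.475 of Step 1. Kolmogorov-Smirnov power in that setting is 0.15.

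**Step 4: the between-arm reading.** Applying Wilcoxon-Mann-Whitney to change scores, 40 against 80 (5,000 replicates), gives a size of 0.044 to 0.049. That use is valid.

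**The case against.** **The strongest defence** has three parts.

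- *The t test may be paired.* If so, the plan already contains one valid within-person analysis. This stands, and the t test is not faulted here. It does not make the other two tests valid for the same job.
- *Wilcoxon-Mann-Whitney may be meant for change scores between arms.* Power and Sample Size promises comparisons of intervention with control, and Step 4 shows that this use holds its size. The reading can rescue the sentence on questionnaire scores. It cannot rescue the other sentence, whose stated purpose is to compare time points.
- *The consequences are limited.* This stands too. The outcomes are secondary and exploratory, estimates with 95% CIs and effect sizes are also planned, and with positive correlation the error does not inflate false claims of change.

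That the article is condensed does not remove the problem. The tests are named, so a fuller plan that used paired methods would have to contradict this text.

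**Stronger readings that the protocol does not support**

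- A reader might infer that most of the power is lost. Step 3 gives losses from about 1% to 88%. More than half is lost only for the 0.3 SD change, with ρ of about 0.5 or more at n=40 or about 0.7 or more at n=80.
- A reader might infer that all three tests are run on every comparison, so that picking the best inflates the false-positive rate. The text lists the tests without saying that each applies to every outcome, and the same sentence promises a multiplicity correction.
- A reader might infer that the confidence intervals are too wide. The CIs are planned for means, medians and lower quantiles; nothing says they are derived from these tests.
- A reader might object to Kolmogorov-Smirnov on short ordinal scales. The sentence on questionnaire scores names only t and Wilcoxon-Mann-Whitney.

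**Conclusion.** The point holds in limited form. As written, two independent-sample tests are assigned to paired data, which is a wrong rule and not merely a missing detail. That much follows from the text without any calculation.

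The size rests on assumptions. For ρ from 0.3 to 0.7 at n=40, a nominal 0.05 test has a true size of 0.018 down to 0.001 (Wilcoxon-Mann-Whitney) or 0.025 down to 0.005 (Kolmogorov-Smirnov). The effect on power runs from negligible (n=80, 0.5 SD) to severe (n=40, 0.3 SD, high ρ), and the protocol does not say where in that range the trial falls. The direction is conservative as long as the within-person correlation is positive, which is the usual case for repeated scores.

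The correction is worth making because it is simple and the within-person results are part of the preliminary evidence on efficacy. It does not threaten the primary feasibility objective and should not be ranked as a major flaw.

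**What to change.** Replace the time-point sentence in the Statistical Analysis Plan section with wording such as: *Within-person comparisons of time points use the paired t test, or the Wilcoxon signed-rank test for ordinal or clearly non-normal scores, or a mixed model for repeated measures. One test is named in advance for each outcome, and the confidence interval of the paired difference is reported. The Wilcoxon-Mann-Whitney and Kolmogorov-Smirnov tests are used only between independent groups, including comparisons of change scores between arms.*

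The sentence on questionnaire scores should say which of the two it means: change within a group, or change compared between arms.

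The Kolmogorov-Smirnov test need not be dropped, since it is valid between groups. The cost is a small wording change, with no new data and no effect on sample size. The Discussion already provides for amending the protocol. If the time-point tests have already been run, they can be repeated on the same data and the change declared in the report.

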### Eligibility Criteria

Inclusion criteria are as follows: (1) 16 years or older, (2) affected by persisting health problems beyond 4 weeks after SARS-CoV-2 infection (confirmed either by polymerase chain reaction or rapid antigen testing), (3) personal reporting of subjective cognitive symptoms such as brain fog and fatigue ≥5/10 on a Likert scale, (4) having access to an appropriate technical device to participate in the intervention (eg, PC, tablet, or smartphone with internet access), and (5) provision of written informed consent to participate in the study (in clients <18 years of age, additional written consent is to be provided by legal guardians). Individuals not meeting the above-mentioned inclusion criteria and those lacking the willingness or ability to complete the program consisting of either teletherapy or video sessions will be excluded from the study.

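### The Statistical Analysis Plan section ties its outcome tests to time points and never to the randomised groups whose comparison the protocol promises

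*Protocol article*

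**What the plan says.** The Study Design section describes a randomised trial of two intervention arms "in comparison to a control group (group 3: watch and wait"), and gives preliminary evidence on efficacy as one of its purposes. Power and Sample Size then states that "exploratory analyses will address potential differences in outcomes of cognitive function, QoL, occupational performance, and social participation between the intervention and control groups". It also limits the weight of these analyses: "efficacy analyses with regard to secondary outcomes will only be exploratory", and "The pilot study is not sufficiently powered to evaluate the effectiveness of the intervention".

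The Statistical Analysis Plan section is fairly specific. It names software, an analysis population ("An intention-to-treat approach will be used"), estimates with 95% CIs for means, medians and lower quantiles, effect sizes, and tests. The tests on outcomes come in two sentences. The first has the stated purpose of comparing time points, and there the t, "Wilcoxon-Mann-Whitney, and Kolmogorov-Smirnov tests will be applied, including corrections for multiple testing". The second begins "Scores derived from questionnaires will be analyzed concerning change over time using" and names the t and Wilcoxon-Mann-Whitney tests. The only other tests ask whether factors such as age or education affect the feasibility of the therapy. No sentence in the section names the randomised group as the thing compared.

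**The concern.** A randomised control arm exists to show what would have happened without the intervention. Change from T0 to T1 within an intervention arm does not show that. Three features of this trial make change without treatment plausible:

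- People may enter from 4 weeks after infection, when spontaneous recovery is possible.
- Entry requires "personal reporting of subjective cognitive symptoms such as brain fog and fatigue ≥5/10 on a Likert scale". Selecting on a high self-reported score invites regression to the mean, most directly on that item and on measures correlated with it.
- Table 1 schedules the Wilde-Intelligence test and the d2 test at enrollment, week 12 and week 24, so practice effects can enter.

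All three should act alike in every arm, and only the contrast with watch-and-wait removes them. If the section is followed as written, the reported efficacy signal could be a before-after change, and a later trial could be planned on it.

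**Working it through.** **Setting the sections side by side**

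| Section | Contrast stated | Test or estimate attached |
|---|---|---|
| Study Design | two intervention arms against watch-and-wait | none |
| Power and Sample Size | intervention against control, exploratory | none |
| Statistical Analysis Plan, first test sentence | time points | t, Wilcoxon-Mann-Whitney, Kolmogorov-Smirnov |
| Statistical Analysis Plan, second test sentence | change over time | t, Wilcoxon-Mann-Whitney |

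The promised contrast has no test, and the tests have a different contrast.

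**Size of the risk.** The article states no alpha, recovery rate, SD or correlation, so there is no figure to reproduce and what follows is an illustration.

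- From the document: intervention arms of 40 and a control arm of 80 (Intervention Delivery).
- Assumed: zero treatment effect; the same improvement *g* (in SD units) in every arm; pre-post correlation *r* of 0.5 to 0.7; two-sided 0.05 without correction; complete follow-up.

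SD of change = √(2(1−*r*)), which is 1.000 at *r* = 0.5 and 0.775 at *r* = 0.7. The noncentrality of the paired t test is *g*√*n* / √(2(1−*r*)). For *n* = 40 and *g* = 0.3 this is 0.3 × 6.325 / 1.000 = 1.90 at *r* = 0.5, and 0.3 × 6.325 / 0.775 = 2.45 at *r* = 0.7. The noncentral t distribution with 39 degrees of freedom gives 46% and 67%.

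| Common improvement *g* | Paired test, 40-person arm | Paired test, 80-person control arm |
|---|---|---|
| 0.2 SD | 24-36% | 42-63% |
| 0.3 SD | 46-67% | 76-93% |
| 0.5 SD | 87-98% | 99-100% |

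**Effect of the stated multiplicity correction.** The method is not given. Taking Bonferroni over the six secondary instruments in Table 1 as an example (0.05/6 = 0.0083), the figures for the 40-person arm fall to about 8-14%, 21-38% and 65-90%.

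**Between-group test.** The expected difference in change is *g* − *g* = 0 whatever *g* is. In a simulation of 4,000 runs per setting, a test of change between arms (40 v 80, and 80 v 80) was significant in about 4-6% of runs for *g* from 0 to 0.5.

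**Fit of the named tests to paired visits.** An independent-samples test ignores the correlation between visits and so overstates the variance of the difference. In the same simulation, with no change at all, Wilcoxon-Mann-Whitney applied to T0 and T1 of one 40-person arm rejected in 0.2-0.6% of runs instead of 5%, and Kolmogorov-Smirnov in 0.2-0.5%.

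**The case against.** The strongest reply is that the protocol does commit to comparing intervention with control. A reader might infer that the trial cannot answer that question, or that the control arm is recruited and then left unused. The documents do not support this: the intent is stated under Power and Sample Size, and what is missing is its link to the tests.

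Second, Wilcoxon-Mann-Whitney and two-sample Kolmogorov-Smirnov are independent-samples tests, so the second test sentence could mean that change scores are compared between arms. That reading is possible for change scores. It does not fit the first test sentence, whose stated purpose is to compare time points, and a plan open to both readings needs correcting.

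Third, a reader might infer that natural recovery will be mistaken for benefit. That is a conditional risk. Recovery must occur, and within-arm change must be read as effect although a concurrent control is followed. The document gives no recovery rate, and at 0.1 SD with *r* = 0.6 the uncorrected figure for a 40-person arm is only 11%.

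Fourth, the item list in the analysis section might be read as dropping occupational performance. That list covers T0, T1 and T2, whereas Table 1 schedules the COPM only at enrollment and week 12, so its absence fits the schedule. The Wilde-Intelligence memory measure has all three visits and is not named in the list, so that small gap stands.

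Finally, missing-data rules are commonly left to a fuller plan, and their absence from an article is no finding. The same holds for the choice of model. Feasibility is primary and efficacy exploratory, which limits the weight of the point but does not remove the mismatch.

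**Conclusion.** The point holds as a mismatch within the protocol article. An intervention-versus-control comparison is promised, every outcome test is framed by time, and the named rank and distribution tests do not suit paired visits. This goes beyond detail left to a fuller plan, because the section does state a contrast and it is not the randomised one. The percentages depend on the assumed improvement and correlation and on reading the tests as paired and uncorrected; they show direction and rough scale and do not predict this trial's results. No confirmatory conclusion rests on these analyses, so it is a should-fix and not a must-fix.

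**What to change.** In the Statistical Analysis Plan section:

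- State that each secondary outcome is compared between randomised groups (teletherapy v control, video v control, teletherapy v video) at T1 and T2. Adjust for the outcome's baseline value, by ANCOVA or by a mixed model with group-by-visit terms, and report differences with 95% CIs.
- Analyse the COPM at week 12 only, and name the Wilde-Intelligence test among the analysed outcomes.
- Keep within-group change as description, without a claim of effect. If it is tested at all, use paired methods.
- Keep the label exploratory.

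A therapist random effect and adjustment for time since infection are optional. For the latter, confirm first that infection dates are recorded: Table 1 lists infections but gives a time point only for vaccination.

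The cost is wording and a few lines of R, with no new data. At the stated arm sizes the unadjusted 95% CI half-width is 1.96 × √(1/40 + 1/80) = 0.38 SD for one intervention arm against control, and 1.96 × √(2/40) = 0.44 SD between the two intervention arms. Baseline adjustment multiplies these by √(1−*r*²), giving about 0.27-0.33 SD and 0.31-0.38 SD for *r* from 0.7 down to 0.5, if follow-up is complete. That is adequate for an exploratory estimate.

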**Results:**

The German Ministry of Education and Research provided funding for this research in March 2022. Data collection took place from October 2022 to August 31, 2023. Data analysis will be completed by the end of April 2024. We anticipate publishing the results in the fall of 2024.

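### The protocol promises comparisons with the control group, but its Statistical Analysis Plan ties the efficacy tests only to time points and names no contrast between arms

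*Protocol article*

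**What the plan says.** Study Design sets the two therapy groups "in comparison to a control group (group 3: watch and wait"). Power and Sample Size adds that "exploratory analyses will address potential differences in outcomes of cognitive function, QoL, occupational performance, and social participation between the intervention and control groups". It gives no test, contrast or time point for this.

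The tests are named in the Statistical Analysis Plan section, with two stated purposes for the efficacy scores:

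- "To compare time points, *t*, Wilcoxon-Mann-Whitney, and Kolmogorov-Smirnov tests will be applied, including corrections for multiple testing".
- For questionnaire results, t and Wilcoxon-Mann-Whitney are named, again with multiplicity correction. The purpose is put in these words: "Scores derived from questionnaires will be analyzed concerning change over time using".

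The only other tests there relate factors such as age or education to how therapy was experienced. The section also says "An intention-to-treat approach will be used" and that effect sizes will be computed, without saying from which contrast.

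**The concern.** The stated aim and the stated method do not match. The aim is a comparison with a randomised control group, but no test, interval or effect size for an efficacy score is said to take the randomised arm as its factor.

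This matters because the design gives several reasons for scores to move without any therapy:

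- **Practice.** Table 1 repeats the same attention test and the same intelligence-test modules at enrollment, week 12 and week 24.
- **Natural recovery.** Entry is possible from 4 weeks after infection.
- **Regression to the mean.** Entry requires a self-rating of at least 5 out of 10, so outcomes that correlate with that rating will tend to move back.

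The watch-and-wait arm is exposed to the same influences, and a contrast with it removes them. A test of T0 against T1 or T2 does not. Study Design also states the aim of obtaining preliminary evidence on efficacy. Effect sizes taken from change within an arm would carry the shared change into the planning of a later trial.

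**Working it through.** **Plan's own figure.** There is none to reproduce. The sample of 120-150 is described as pragmatic, with no alpha, effect size, SD or correlation behind it.

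**Inputs from the protocol.** Intervention Delivery gives 40 for teletherapy, 40 for video and 80 for control. Smaller arms would lower the within-arm percentages below.

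**Assumptions, none given in the protocol.** Two-sided alpha 0.05; no therapy effect; a shift d common to all arms of 0.2, 0.3 or 0.5 baseline SD; within-person correlation r of 0.5 or 0.7; no dropout.

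**Step 1: within-arm test of T0 against T1, uncorrected.** The SD of change is sqrt(2(1−r)), which is 1.000 at r = 0.5 and 0.775 at r = 0.7. The noncentrality is d × sqrt(n) / SD of change. For n = 40, d = 0.2 and r = 0.7 it is 0.2 × 6.325 / 0.775 = 1.63. The critical value of t on 39 degrees of freedom is 2.023. The noncentral t distribution then gives the chance of a significant improvement:

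| Shared shift | n = 40, r = 0.5 | n = 40, r = 0.7 |
|---|---|---|
| 0.2 SD | 23% | 36% |
| 0.3 SD | 46% | 67% |
| 0.5 SD | 87% | 98% |

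The nominal rate in that direction is 2.5%. A simulation of the paired t test (4,000 trials per scenario, counting significance in either direction) gave 23% and 35%, 46% and 67%, and 87% and 98%.

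**Step 2: with multiplicity correction.** The protocol promises correction but gives neither method nor number of tests. Take Bonferroni over six tests, one per secondary instrument in Table 1. Alpha becomes 0.05 / 6 = 0.0083, and the critical value on 39 degrees of freedom rises to 2.78:

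| Shared shift | n = 40, r = 0.5 | n = 40, r = 0.7 |
|---|---|---|
| 0.2 SD | 8% | 14% |
| 0.3 SD | 20% | 38% |
| 0.5 SD | 65% | 90% |

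The nominal rate in that direction is now about 0.4%. Correction lowers the rates but does not remove a shift that is really there.

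**Step 3: the named independent-sample tests, applied to T0 against T1 in the same 40 people.** In the simulation, the unpaired t and Wilcoxon-Mann-Whitney tests rejected in 0-0.6% of trials with no shift, because they ignore the pairing. With a shared shift of 0.5 SD they rejected in 60-66%. So they are mis-sized with no shift and, like the paired test, respond to shared change.

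**Step 4: change compared between arms, 40 against 80, uncorrected.** In the same simulation the t and Wilcoxon-Mann-Whitney tests on change scores rejected in 4.4-5.5% of trials in every scenario, from no shift to 0.5 SD.

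**The case against.** A reader might infer that the plan contains no comparison of the randomised arms at all, and that non-treatment change will therefore be reported as efficacy. The documents do not support that. Power and Sample Size belongs to the same Analytical Approach section and commits to intervention-versus-control comparisons. The Statistical Analysis Plan section never says that tests are run within arms, and it invokes intention-to-treat. The two sections can be read together, one giving the contrast and the other the tests. Wilcoxon-Mann-Whitney applied to change scores would be a between-arm test. This stands: the text is open to two readings, and the harm arises only under one of them.

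A reader might also fear that a therapy arm will be significant while the control arm is not. Uncorrected, the chance that at least one therapy arm is significant and the control arm is not is (1 − (1 − p40)²)(1 − p80). That is 22-24% at 0.2 SD, but 6-17% at 0.3 SD and under 1% at 0.5 SD, where the control arm is nearly always significant too and exposes the artefact. The risk is real for small shifts only.

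Two mechanisms need limits. The entry rating is not itself an outcome in Table 1, so regression to the mean acts only through correlation with it. Season could be suspected because "Data collection took place from October 2022 to August 31, 2023", but nothing in the protocol shows that season affects these outcomes, so the point does not rest on it.

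Finally, efficacy is declared exploratory and underpowered, and a separate analysis plan may define the contrasts. That lowers the severity but does not remove the point. The article does name tests, and the purpose it gives them does not serve its stated aim.

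**Conclusion.** The point holds as a mismatch between two parts of one section: comparisons with control are promised, while the efficacy tests are tied to time points, with no arm contrast and with some tests unsuited to repeated measures. Run as written, the plan can turn change shared by all arms into apparent efficacy. Depending on the assumed shift and correlation, an arm of 40 would show this in 23% to 98% of trials uncorrected, or in 8% to 90% under the assumed six-test Bonferroni correction. The between-arm test holds about 5% uncorrected.

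The direction does not depend on the assumptions; the size does, because the protocol gives no shift, SD or correlation. Severity is moderate: feasibility is the primary objective and efficacy is secondary and exploratory.

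**What to change.** State in the Statistical Analysis Plan section that the exploratory efficacy estimate for each secondary outcome is the between-arm difference in change from T0, for teletherapy versus control and for video versus control, with a 95% CI. Give it at T1 and T2, except for the Canadian Occupational Performance Measure, which Table 1 schedules only at enrollment and week 12 and which can therefore be compared at T1 only. Compute effect sizes from these differences. If Wilcoxon-Mann-Whitney is kept, say that it is applied to change scores between arms. Report within-arm changes descriptively, and do not cite them as evidence of efficacy.

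The cost is wording only, with no new data or visits. The downside is fewer and less striking p-values.
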